| Exposures, Outcomes and CovariatesExposure: breast cancer Women will be considered exposed at the day of the breast cancer diagnosis (index date), denoted by the first entry of one or more of the Read codes provided in appendix 2. Primary outcomes: anxiety and depression To our knowledge, there is no validated list of Read codes to identify anxiety and depression in the CPRD GOLD primary care database. Algorithms will be developed and tested to identify anxiety and depression cases in CPRD. The algorithms will be chiefly determined by clinical diagnoses of anxiety and depression registered in the EHR with Read codes, and supplemented with information from drug prescriptions, referrals, and symptoms (if deemed suitable). Please see section N, plan of analysis for specific aim 1, for more details on the construction and validation of algorithms. Secondary outcomes: fatigue, mild cognitive impairment, pain, sleep disturbance, sexual dysfunction, and fatal and non-fatal self-harm Similarly, we will develop and test outcome-specific algorithms that identify events using a hierarchy of data on clinical diagnoses, prescriptions, referrals and symptoms.  In sensitivity analysis, we will consider linked data (see section J for data linkage requested) to develop more precise definitions of the outcomes, when possible. For example, two definitions of suicide will be considered: (1) considering Read codes only to identify suicides in CPRD; (2) considering Read codes for suicide as well as death registration data where suicide was recorded as primary cause of death (ICD-10 codes provided in appendix 3) Covariates Variables considered as potential confounders or effect modifiers of the association between breast cancer history and anxiety and depression (the primary outcomes of this study) are described below. The directed, acyclic graph (DAG) in appendix 4 explicitly describes the assumptions of the causal relations between the variables that underpin the choice. Please refer to the data analysis (section N) for details on which variables will be considered for sensitivity analyses only. *Potential confounders*  - Age at diagnosis (categorical variable, in 10-year age bands)   Defined as the absolute difference between the year of breast cancer diagnosis and year of birth. Age is a strong risk factor for breast cancer and for mental disorders.   - Alcohol drinking habits at diagnosis (categorical variable: current drinker, former drinker, never drinker)   Excess alcohol drinking is a well-established risk factor for breast cancer [30], besides being positively associated with anxiety and depression [31-33]. The most recent data on alcohol drinking habits prior to index date will be used in analysis. Current drinking will be further sub-divided into high, moderate, low or unknown intake of alcohol.   - Body mass index at diagnosis (categorical variable: underweight, normal weight, overweight, obesity class I, obesity class II and above)   Calculated as BMI=(weight/height^2^). Higher body mass index is protective against breast cancer in pre-menopausal women, but a risk factor for breast cancer post-menopause [34]. Obesity increases the risk of anxiety and depression [35, 36]. The most recent recording of BMI prior to index date will be used in analysis. The BMI values will be categorised into 5 categories: <18.5 kg/m^2^ (underweight), 18.5-24.9 kg/m^2^ (normal weight), 25.0-29.9 kg/m^2^ (overweight), 30.0-34.9 kg/m^2^ (obesity class I), ≥35.0 kg/m^2^ (obesity class II and above). Read codes for body weight categories recorded in the year prior to the breast cancer diagnosed will be considered to supplement missing information for this variable.   - Calendar period of diagnosis (categorical variable: ≤1994; 1995-1999; 2000-2004; 2005-2009; 2010-2014; >2014)   Even though calendar time *per se* does not change the risk of breast cancer, the risk of being diagnosed with breast cancer changed over time, probably due to increase awareness of the disease along with widespread use of mammography to screen for breast cancer. Time has also contributed for mental disorders being more likely to be diagnosed, due to raises awareness and increased recognition of the importance of mental disorders among health care professionals.   - Diabetes mellitus (dichotomous variable: yes/no)   Diabetes mellitus has been associated with an increased risk of breast cancer [37] and depression [38]. Algorithms previously defined elsewhere will be applied to identify patients with diabetes mellitus in the CPRD GOLD primary care database [39, 40].   - Level of deprivation (categorical variable: quintiles of patient-level IMD).   The IMD is an ecological measure of deprivation for small areas in England that combines information from seven domains (income, employment, education, health deprivation, crime, barriers to housing, and living environment), and ranks the small area from 1 (most deprived) to 32,844 (least deprived). Patients will be categorised in quintiles of IMD, with quintile 1 representing those least deprived and quintile 5 those most deprived.   - Menopausal status (dichotomous variable: premenopausal/postmenopausal)   Menopausal status is a potential confounder of the association between breast cancer history and depression, as the risk of breast cancer increases with menopause [30], and so does the risk of depression [42]. However, information on menopausal status is not easily available in the CPRD database. We will therefore produce results stratified by an age cut-off, as a proxy of the menopausal status of the women. The cut-off will be the mean/median age at natural menopause in the UK.   - Smoking history at diagnosis (categorical variable: current smoker, former smoker, never smoker)   Information on Read codes available on the data will be used to classify patients by smoking history. The most recent data on smoking prior to index date will be used in analysis. *Potential effect modifiers*  - Living alone (dichotomous variable: yes/no)   Ascertained from the CPRD GOLD primary care data using Read codes (list provided in [41]) and the patient’s family number (variable ‘famnum’ from the patient file). Women living in household of <2 people will be classified as living alone.   - Residing in a care home (dichotomous variable: yes/no).   This variable will be defined from the CPRD GOLD primary care database, using Read codes (list provided in [41]), and information gathered in the family number variable (‘famnum’). For the latter, ‘care home’ will be defined as a household with >3 individuals aged ≥65 years and if their total count was more than of individuals <65 years.   - Ethnicity (categorical variable: White, South Asian, Black, Others and mixed)   Ethnicity data recorded in the CPRD GOLD primary care database will be categorised in five groups, following the categories defined in the UK 2011 Census: White, South Asian, Black, Others and mixed. This variable will be derived from Read codes available in the CPRD GOLD primary care database and from HES, since the combined data sources increase completeness from 55% to 79% [41]. For analysis, four groups will be considered: White, South Asian, Black, Others and mixed.   - Previous mental health history (categorical variable: yes/no)   Mental health history will be defined as having had an episode of anxiety- or depression-related disorders (primary outcomes) or any the secondary outcomes, ever recorded at more than 1 year before the breast cancer diagnosis (patients who had the outcome in the year before the breast cancer diagnosis will be excluded from the cohort). These will be identified based on the algorithms defined in aim 1 of this study.   - History of stroke or coronary heart disease at diagnosis (two dichotomous variables: yes/no)   These will include ischaemic heart disease (angina and myocardial infarction) and stroke, which are amongst the leading causes of disability-adjusted life years in females in the UK. These will be identified through Read codes recorded in the CPRD GOLD primary care database.   - Socioeconomic status (IMD quintiles of deprivation)   The IMD is an ecological measure of deprivation for small areas in England (Lower Super Output Areas). It combines information from seven domain indices (income, employment, education, health deprivation, crime, barriers to housing, and living environment). The index ranks the areas from 1 to 32,844; usually the quintiles are used for research purposes: from 1 (most deprived) up to 5 (least deprived). The IMD is linked to the primary care data using the postcode of the patient or practice. *Potential mediators of the association between breast cancer history and anxiety/depression*  - Sequelae from cancer treatments (six separate binary variables (yes/no): lymphoedema, pain, mild cognitive impairment, fatigue, sexual dysfunction, sleep disorder)   Lymphoedema will be defined using Read codes for the condition, in the CPRD GOLD primary care database. Pain, mild cognitive impairment, fatigue, sexual dysfunction, and sleep disorder are secondary outcomes of this study, and will be identified based on the algorithms defined in aim 1 of this study. Patients will be classified as having had one of these conditions if there was more than one record for these conditions within a 6-month interval.   - Exposed to endocrine treatment for breast cancer: binary variable (yes/no).   This will be defined from the CPRD GOLD primary care database using Read codes for at least two prescriptions of anastrozole, tamoxifen, exemestane, or letrozole [43] within a 6-month period. |

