| Data/ Statistical AnalysisPrimary analysesSpecific aim 1. To develop and validate algorithms to identify patients with anxiety and depression Algorithm development  A systematic review is currently under way to identify the lists of Read codes previously used to define anxiety and depression of primary care databases in the UK. The systematic review search expressions are provided in appendix 5.  *(A) Raw data tabulations*  We will estimate the number and proportion of patients recorded during the observation period with:   1. Diagnostic Read code for anxiety/depression; 2. Prescription of anxiolytics/antidepressants; 3. Referred to mental health services; 4. Symptoms of anxiety/depression.   Proportions will be estimated by calendar year.  *(B) Simpler algorithm*  We will estimate the additional contribution of prescriptions, referrals and symptoms to identify cases of anxiety/depression in CPRD. Referrals and prescriptions of anxiolytics/antidepressants will be considered as sufficient to identify cases of anxiety/depression if a Read code for symptoms of anxiety/depression, respectively, were recorded during the previous year. The reasons for this are threefold: (1) there is good evidence that GPs switched from anxiety/depression diagnostic codes to symptomatic ones [44, 45], following claims of over diagnosis of these conditions; (2) antidepressants and anxiolytics have also other indications, including anxiety disorders for antidepressants [46], which raise questions of the use of these data their own to identify these outcomes; (3) pharmacological treatment of mild depression has been discouraged since 2004 [47], and thus referrals to psychotherapy may help to capture milder cases.  *(C) Complex algorithm*  A more detailed algorithm will be developed considering that some drugs are prescribed for both depression and anxiety, in addition to manage vasomotor symptoms, which may be more frequent in breast cancer survivors than in women who did not have cancer. An example for depression is given in appendix 6. We will estimate the number of patients with anxiety/depression at each step, to evaluate how much each category adds to what has been previously recorded.  Algorithm validation  A random sample of 1 million patients of both sexes will be selected from the CPRD GOLD primary care database. We will apply each algorithm and produce descriptive statistics stratified by likelihood of having the outcome, including:   - Number and proportion of patients with the anxiety, depression or both, by 3-year calendar period; - Number and proportion of patients with the anxiety, depression or both, by 3-year calendar period, age and sex; - Number and proportion of patients with the anxiety and depression by 3-year calendar period and country in the UK.   For each outcome, we will compare the estimates obtained with others obtained from the literature, prioritising national surveys of population-based data such as the following:   - Adult Psychiatric Morbidity Survey 2007 [48] and 2014 [49]; - Measuring National Well-being programme, made available by the Office for National Statistics (includes prevalence of those in the UK with some evidence indicating depression or anxiety, since 2013, by country in the UK and English regions, and by 10-year age groups up to 75 years) [50].   The final algorithm will be chosen by considering information in the numeric value closer to the estimates obtained from the literature. Sensitivity analysis Proportion estimates considering the presence of symptomatic codes within the previous year will be re-calculated to consider shorter periods of time (i.e. 3 and 6 months). Specific aim 2. Risk of mental health outcomes in women who had breast cancer compared to women who did not have cancer**Primary outcomes analysis – depression and anxiety**Main analysis Descriptive statistics including number of events observed and person-years at risk will be computed, overall and stratified by the covariates listed in section M (see above). Medical procedures for the diagnosis of breast cancer are likely to cause anxiety. To deal with this we planned to exclude patients who had a record of anxiety diagnosed within 1 year before the breast cancer; this could result in patients with higher levels of trait anxiety being excluded from the analysis. We will calculate the number and proportion of patients who were excluded because they had the outcome in the year prior to the breast cancer, stratified by month. We will also describe how many of those who were excluded from analysis had an outcome after the breast cancer diagnosis by age-group. The quintiles of the distribution of the number of consultations (defined using the ‘consid’ variable) will be described, as this can indicate the patterns of seeking care between women with a history of cancer, compared to those who did not.  The association between breast cancer history and anxiety and breast cancer history and depression, will be quantified using Cox regression models with time since index as the underlying time scale, and stratifying on matched set to account for matching by age and primary care practice. Follow up will begin at the index date (vide section M for definition of the exposure) and will terminate when an outcome is observed. Women will be censored at the earliest date of any of these: cancer recurrence, other cancer diagnosis, death, transference out of the practice; if these events don’t occur, censoring will be observed at the date of last data collection for the practice. Crude measures of the association between breast cancer history and anxiety and depression will be reported stratifying by the covariates described in section M.  Cox multivariate regression analysis will be use to estimate hazard ratios adjusted for calendar period of breast cancer diagnosis, menopausal status, and diabetes mellitus at baseline (see list of confounders in section L, covariates, for the definition of these variables).  Interaction terms between the exposure and the following variables will be added, to explore effect modification by ethnicity (White, South Asian, Black, Others and mixed), place of residence (care home vs. household), co-habitation status (living alone vs. cohabiting), SES (quintiles of IMD), having mental health disorders history (yes vs. no), having history of stroke (yes vs. no) and coronary heart disease (yes vs. no).  Confidence intervals will be calculated using robust estimates of the standard errors, to account for the fact that patients may also contribute with time at risk in the unexposed cohort prior to their cancer diagnosis.  The proportional hazards assumption will be tested in two ways: 1) graphically, by plotting the cumulative rates on a log scale; 2) inferentially, by applying a likelihood ratio test to the estimates obtained for the entire period of observation and for time split into intervals. Sensitivity analyses Sensitivity analyses planned for this study will include a subset of patients only; this is because they use variables from linked data, which is available for a fraction of the patients only, and include variables amenable to have missing data (i.e. BMI, alcohol intake, smoking and patient-level IMD). Regarding the latter, we will quantify the completeness of each variable to decide on their inclusion in the final models. Analyses including variables with missing data will be restricted to patients with complete data for covariates (complete case analysis), if missing data is likely to be missing not a random. The following sensitivity analyses are planned:   1. The main analysis will be repeated further adjusting for age at diagnosis (continuous variable, since matching allowed for 3-year gap), patient quintile level of IMD, alcohol drinking patterns prior to index date, smoking history and body mass index categories prior to index date. 2. We will exclude women diagnosed with the outcome of interest in the year prior to the cancer diagnosis. To account for the fact that treatment for these conditions may often last for more than one year, and that mild anxiety and depression may be treated in psychological services and not result in visits to the GP, we will repeated the main analysis including only patients who had 5 years of complete follow up prior to the index date and did not have the outcome recorded at any point during this period.  Multiple comparisons We acknowledge that this study includes multiple comparisons for each outcome, and several outcomes. Thus, P-values in the range ~0.01-0.05 be considered as some statistical evidence of an effect and interpreted cautiously. Sample size considerations considering a 0.01 probability of type I error (α) are provided in see section I. Specific aim 3. To estimate association between breast cancer history and anxiety/depression by presence of lymphoedema, pain, mild cognitive impairment, fatigue, sexual dysfunction, sleep disorders, and having done endocrine therapy, during the follow up period. We will estimate the cumulative incidence and period prevalence of lymphoedema, pain, mild cognitive impairment, fatigue, sexual dysfunction, and sleep disorders, in breast cancer survivors during the overall follow up period and by 5-year of follow up period.  We will estimate the hazards of developing anxiety and depression (the main outcomes) for three groups of patients: 1) breast cancer survivors who did not develop the common complication (i.e. lymphoedema, pain, mild cognitive impairment, fatigue, sexual dysfunction, sleep disorders) up to time *t*; 2) breast cancer survivors who have had the common complication at time *t*; 3) women who never had cancer. A Cox regression model will be used to estimate the association between time-updated exposure and the main outcomes (anxiety and depression), having as reference the hazard observed for the women who did not have cancer. The exposure variable will be time-updated; this means that women who develop a common complication will contribute with information to group 1 until the date at which they develop the complication of interest; after this point they will contribute with information to group 2. All models will be adjusted for calendar period of breast cancer diagnosis.  Confidence intervals will be calculated using robust estimates of the standard errors. Sensitivity analyses planned in objective 2 will be applied to this objective as well. Secondary outcomes analyses – fatigue, mild cognitive impairment, pain, sleep disturbance, sexual dysfunction, fatal and non-fatal self-harm The steps outlined above will be repeated for the secondary outcomes. Sensitivity analysis will follow the same rationale as described for the primary analysis. |

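### The main aim 3 models leave out prior anxiety and depression, which may exaggerate the hazard ratio for survivors with a complication

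*Protocol*

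**What the plan says.** **Model.** Under Data/Statistical Analysis, Specific aim 3, the protocol plans: "A Cox regression model will be used to estimate the association between time-updated exposure and the main outcomes (anxiety and depression"). The exposure has three levels: survivors who have not yet had the complication (group 1), survivors who have had it (group 2), and women without cancer. Both survivor groups are compared with the last, "having as reference the hazard observed for the women who did not have cancer". Survivors move from group 1 to group 2 when the complication is recorded.

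**Adjustment.** The set is stated in one sentence: "All models will be adjusted for calendar period of breast cancer diagnosis". For comparison, aim 2 reports "hazard ratios adjusted for calendar period of breast cancer diagnosis, menopausal status, and diabetes mellitus".

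**Prior mental health.** The Covariates section lists this among the potential effect modifiers: "Mental health history will be defined as having had an episode of anxiety- or depression-related disorders (primary outcomes) or any the secondary outcomes". The variable has a time window, so that an episode counts only if it was "ever recorded at more than 1 year before the breast cancer diagnosis". Its one named use is an aim 2 interaction term: "having mental health disorders history (yes vs. no"). The confounder list in that section is drawn up for breast cancer history as the exposure. No list is given for the contrast between survivors with and without a complication.

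**Other provisions.** The study population section excludes severe mental illness before diagnosis and the analysed outcome in the year before diagnosis. Sensitivity analysis 2 restricts to women with 5 years of prior follow-up and no record of the outcome in that time. The aim 2 sensitivity analyses are carried over to aim 3. The Covariates section labels the complications and endocrine therapy as potential mediators.

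**The concern.** Aim 3 splits survivors by something that happens after diagnosis and is recorded when a woman consults. A woman with earlier anxiety or depression is plausibly more likely to have fatigue, pain, sleep disorder or sexual dysfunction recorded, and more likely to have a new episode. Her history then acts as a common cause of group 2 membership and of the outcome.

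The design does not deal with this. Matching on age and practice pairs survivors with controls; it cannot balance history between survivors with and without a complication. Calendar period is no substitute. If the imbalance is material, part of what aim 3 reports as the added hazard among women with a complication would be vulnerability that predates the cancer. Because the protocol calls the complications potential mediators, readers are likely to take the result causally. A large sample does not reduce this bias.

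**Working it through.** There is no planned figure to reproduce: Table 2 covers survivors against controls, not aim 3. The check has two parts.

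**1. Who remains with unadjusted history**

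| Provision | What it removes | What it leaves in aim 3 |
| --- | --- | --- |
| Severe mental illness exclusion | The severe disorders listed | Anxiety and depression |
| 1-year exclusion | Analysed outcome in the year before index | Older episodes; the other primary outcome at any time |
| Sensitivity analysis 1 | Adds age, deprivation, alcohol, smoking, BMI | No mental health term |
| Sensitivity analysis 2 | Analysed outcome over 5 years | Episodes before that; the other primary outcome; the main estimate unchanged |

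So prior depression can remain in the anxiety analysis, and the reverse.

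**2. Possible size**

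The bias from one omitted binary covariate, with no true effect of the complication, is approximately

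B = [1 + p1(RR − 1)] / [1 + p0(RR − 1)],

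where p1 and p0 are the prevalences of prior anxiety/depression in the two groups compared and RR is the effect of history on the outcome hazard. None of these is in the protocol; all values below are assumptions.

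*Complication versus no complication:*

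| RR | p1 | p0 | Calculation | B |
| --- | --- | --- | --- | --- |
| 1.5 | 25% | 20% | 1.125/1.10 | 1.02 |
| 2 | 40% | 20% | 1.40/1.20 | 1.17 |
| 3 | 40% | 20% | 1.80/1.40 | 1.29 |
| 4 | 50% | 25% | 2.50/1.75 | 1.43 |

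*Each group against women without cancer.* Assume history in 25% of survivors and 25% of controls, a complication in 30% of survivors, a history–complication odds ratio of 2, and RR 3. Solving gives p1 = 34.6% and p0 = 20.9% (0.3 × 0.346 + 0.7 × 0.209 = 0.25).

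- Group 2: (1 + 0.346 × 2)/(1 + 0.25 × 2) = 1.692/1.50 = 1.13
- Group 1: (1 + 0.209 × 2)/1.50 = 1.418/1.50 = 0.95
- Ratio: 1.19

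*Allowing for time-updating.* The group 1 figure above treats the groups as fixed. In the planned model every survivor starts in group 1, so its history prevalence begins at that of all survivors and falls as women move to group 2. Take history in 40% of those who ever have a complication, 22% of those who never do, 25% of controls, and RR 3.

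- Group 2: 1.80/1.50 = 1.20.
- Group 1, survivors overall 25%: starts at 1.50/1.50 = 1.00 and ends at 1.44/1.50 = 0.96, so about 0.98 over follow-up.
- Group 1, survivors overall 28%: starts at 1.56/1.50 = 1.04 and ends at 0.96, so the average can fall on either side of 1.
- Group 2 relative to group 1 in the 28% case: 1.20/1.04 = 1.15 at the start and 1.20/0.96 = 1.25 at the end.

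The upward bias in group 2 and the widened contrast persist in both cases. A fixed sign for group 1 does not.

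**The case against.** **Prior history is not ignored.** The 1-year exclusion and the 5-year restriction both act on it, and the latter is explicitly applied to aim 3. This stands in part: they reduce the bias. But they cover only the analysed outcome, and the 5-year restriction is a secondary analysis in a subset.

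**Aim 3 is worded as an association, and the size is unknown.** Both are true. A reader might infer that complications are bound to look like causes of anxiety and depression. The documents do not support that: they give no prevalences or effect sizes, and at the weak end of the assumed range the bias is negligible.

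**A reader might also infer that the group 1 hazard ratio is biased downward.** That holds only for groups fixed at baseline, or where survivors and controls have similar history. With time-updated exposure the effect is small and can reverse.

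**The needed covariate is not ready-made.** A reader might take the protocol's mental health history variable for prior anxiety and depression. It is a single yes/no composite that also counts the secondary outcomes, among them pain, fatigue, sleep disorder and sexual dysfunction. Separate indicators can be built from the aim 1 algorithms, but the protocol does not define them.

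**Adjusting for any record before index would do harm.** The protocol notes that diagnostic procedures for breast cancer are likely to cause anxiety. In the depression model, anxiety from the work-up would stay in the data and be adjusted for as though it were prior history. The protocol's window of more than 1 year avoids this and should be kept.

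**The mechanism is weaker for some exposures.** The common-cause argument is made here for fatigue, pain, sleep disorder and sexual dysfunction. It is less evident for lymphoedema, mild cognitive impairment and endocrine therapy. A common covariate set across the aim 3 models is still reasonable, since the terms precede index and are not on the pathway from complication to outcome.

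**Conclusion.** The point holds as a recommendation to change a stated analysis. The main aim 3 models adjust for calendar period alone, and neither the matching nor the restrictions remove confounding by older episodes or by the other primary outcome. The likely consequence is an upward bias in the group 2 hazard ratio and an exaggerated contrast between survivors with and without a complication.

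The factor of 1.02 to 1.43 for that contrast rests wholly on assumed inputs (RR 1.5 to 4; history prevalences from 25% versus 20% up to 50% versus 25%), so it runs from negligible to material. For scale, Table 2 cites earlier estimates of 1.06 to 1.25 for anxiety diagnoses in survivors against controls; group 2 biases of 1.13 to 1.20, as in the examples, would be of the same order. No direction can be claimed for group 1 without knowing history prevalence in survivors and controls and when complications are recorded.

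**What to change.** In Specific aim 3, add two baseline yes/no covariates to the main models: history of anxiety and history of depression, each recorded more than 1 year before the index date (for controls, the index date of their matched case). Build them separately from the aim 1 algorithms, not from the composite. Report the group 1 and group 2 hazard ratios from this model as the main result, and keep the 5-year restriction as a sensitivity analysis.

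The cost is a change of wording and two derived variables; no linkage or imputation is needed. With a correctly classified indicator, B for this variable becomes 1.00. In practice some confounding will remain: entry requires only 12 months of records, so look-back beyond 1 year varies between women and some history will be missed. The window also leaves the other primary outcome in the final pre-index year unadjusted, which is the price of not adjusting for anxiety caused by the cancer work-up.

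### Aim 3 moves survivors into the complication group with no lag, so anxiety or depression already under way may be attributed to the complication; a lagged analysis and two dating rules would guard against this cheaply

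*Protocol*

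**What the plan says.** Under Specific aim 3 in Data/Statistical Analysis, survivors without the complication form group 1, survivors with it form group 2, and women who never had cancer are the reference. The exposure is time-updated: "women who develop a common complication will contribute with information to group 1 until the date at which they develop the complication of interest", and "after this point they will contribute with information to group 2". The sensitivity analyses for aim 3 are those of aim 2: extra covariates, and a 5-year outcome-free history before the index date.

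The section on covariates lists the complications as potential mediators. It adds that "Pain, mild cognitive impairment, fatigue, sexual dysfunction, and sleep disorder are secondary outcomes of this study", and gives a recording rule: "Patients will be classified as having had one of these conditions if there was more than one record for these conditions within a 6-month interval". It does not say which of the records sets the date.

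For the outcome, "The algorithms will be chiefly determined by clinical diagnoses of anxiety and depression registered in the EHR with Read codes". Candidate algorithm (B) under Specific aim 1 adds a second route: "Referrals and prescriptions of anxiolytics/antidepressants will be considered as sufficient to identify cases of anxiety/depression if a Read code for symptoms" of the condition appears in the preceding year. Whether the symptom code or the later referral or prescription is the event date is not stated. The algorithm itself is still open: "The final algorithm will be chosen by considering information in the numeric value closer to the estimates obtained from the literature".

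**The concern.** A mediator has to come before the outcome it is said to influence. Fatigue, poor sleep, pain, poor concentration and loss of sexual function may be reported while anxiety or depression is emerging and before it is coded as a case. With an immediate switch, such a report moves the woman into group 2, and the event that follows is counted there although the episode began earlier.

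Two errors follow together. Group 2 gains events that the complication did not precede in any real sense, and group 1 loses them. The contrast between the groups then widens even if the complication has no effect, and aim 3 could point to sequelae as drivers of anxiety and depression when the order is partly reversed.

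The plan guards against this at the index date, by excluding women with the outcome in the year before and by testing a 5-year history. It has no equivalent guard at the second time origin, the complication date.

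**Working it through.** **No plan figure to reproduce.** The protocol gives no sample size, power or effect for aim 3. The check shows direction and range only.

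**Inputs from the protocol.** The switch is at the complication date with no lag. The look-back in algorithm (B) is up to 12 months. The reference is women without cancer.

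**Assumed inputs (none is in the documents).** Symptom onset is 0.02 to 0.05 per year and complication rate λ is 0.05 to 0.10 per year, over 5 years of follow-up. A share q of outcomes is dated 0 to 12 months (uniform) after the symptom code. Complication recording is multiplied by k once symptoms start. The true complication effect is a ratio of 1.

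**Method.** 2,000,000 survivors per scenario; the rate ratio of group 2 to group 1 is pooled over 0.1-year bands of time since index (Mantel-Haenszel).

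**Unlagged result, outcome dated at the referral or prescription:**

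| k | q = 0.25 | q = 0.5 | q = 1 |
|---|---|---|---|
| 1 | 1.00–1.01 | 1.00–1.01 | 1.00 |
| 2 | 1.04–1.05 | 1.11 | 1.21–1.23 |
| 3 | 1.09–1.11 | 1.18–1.21 | 1.40–1.46 |
| 5 | 1.18–1.20 | 1.38–1.43 | 1.80–1.94 |

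The k = 1 row shows that delay alone causes no bias. Early symptoms must also raise complication recording.

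**A second set of assumptions.** Outcome 2% per year, 30% of outcomes through the delayed route, the rest with a 3-month prodrome before the diagnosis code, and 10% per year censoring. At k of 2 to 3 the ratio is 1.09–1.19 (complication 3% per year) and 1.13–1.26 (10% per year). A repeat gave 1.08–1.18 and 1.11–1.23. With the q ≤ 0.5 cells above, this gives the range of about 1.04 to 1.26.

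**Against the plan's own reference.** A rerun of the first set with a cancer-free group at the same outcome rate gives, for k of 2 to 3 and q of 0.25 to 0.5, 1.04–1.17 for group 2 and 0.96–0.99 for group 1. Both move, in opposite directions.

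**Effect of the remedies.**
- Dating the outcome at the first symptom code: 0.98–1.02 throughout.
- A 12-month lag with lag time counted in group 1: 0.98–1.02 throughout. A 6-month lag: 0.99–1.26.
- A 12-month lag with lag time as its own category: group 2 against women without cancer is 0.99–1.02 throughout. Against group 1 a small excess remains, because group 1 still loses events to the lag category. The group 1 hazard is multiplied by about (1 − q) + q·A, where A = (1 − e^(−x))/x and x = (k − 1)λ.
  - λ = 0.05, k = 2, q = 0.25: A = 0.975, factor 0.75 + 0.25 × 0.975 = 0.994, ratio 1/0.994 = 1.01.
  - λ = 0.10, k = 3, q = 0.5: A = 0.906, factor 0.5 + 0.5 × 0.906 = 0.953, ratio 1/0.953 = 1.05.
  - λ = 0.10, k = 3, q = 1: factor 0.906, ratio 1/0.906 = 1.10. The rerun gave 1.11.

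**The case against.** **The wording of aim 3 is cautious.** It asks for an association by presence of a complication, and the model's reference is women without cancer rather than group 1. That stands, and it rules out saying that the plan counts such events as caused by the complication. But the complications are labelled potential mediators, and groups 1 and 2 will be compared with each other.

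**A single stray entry cannot move a woman to group 2.** At least two records within 6 months are needed. This also stands: a reader might infer that she switches on the day of any one record, which the text does not say. The rule reduces the problem without removing it, since repeated complaints within one episode also qualify.

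**The 12-month window is only a possibility.** A reader might infer that the outcome is always dated up to a year late. The window belongs to a supplementary route of one candidate algorithm, and arises only if the later event sets the date. Diagnosis-coded cases may have a prodrome too, but the documents give no length for it.

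**A lag has a price.** The protocol's background reports that risk elsewhere was highest soon after diagnosis. A 12-month lag leaves no post-index complication in group 2 during the first year, and counting lag time in group 1 would contradict that group's definition. Lymphoedema is not a symptom of emerging depression, so there is no reason to lag it. All this stands, and it argues against making the lagged model the only one.

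**Lag length could be left to an analysis plan.** Partly. But the protocol itself fixes the switch rule and names the aim 3 sensitivity analyses, and none of them covers this.

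**Conclusion.** The point holds as an unguarded risk of reversed time order. Aim 3 as written has no lag, leaves both the complication date and the outcome date open, and plans no analysis for symptoms that start between the index date and the complication.

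The size is unknown. With no true effect, the group 2 to group 1 ratio is about 1.04 to 1.26 if recording rises two- to threefold and a quarter to a half of outcomes are delayed (or 30% are, with a short prodrome for the rest). It is 1.21 to 1.46 if all outcomes are delayed, and 1.0 if recording does not rise.

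A reader might infer that the ratio could double or triple. That takes stronger assumptions. In the second set at 3% per year, adding complication records to 5%, 10% or 20% of episodes gives about 1.4–1.5, 1.9–2.0 and 2.8–3.3. But the mean window there is 0.3 × 0.5 + 0.7 × 0.25 = 0.325 years, so chance alone puts a record in about 0.03 × 0.325 = 1% of episodes. The required recording rates, −ln(1 − 0.06)/0.00975, −ln(1 − 0.11)/0.00975 and −ln(1 − 0.21)/0.00975, are about 6, 12 and 24 times background. Nothing in the documents supports multiples of that order.

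This is a cheap improvement and does not invalidate aim 3.

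**What to change.** 1. Keep the unlagged aim 3 model as specified.
2. State which record dates the complication. The record that completes the two-record rule is the safer choice, because dating at the first makes group membership depend on a later record.
3. State which record dates the outcome when a case is found by referral or prescription.
4. For fatigue, sleep disorder, pain, mild cognitive impairment and sexual dysfunction, add an aim 3 analysis in which entry to group 2 is lagged by 12 months, with 6 months also shown. Hold the lag time as a separate category, neither group 1 nor group 2.
5. Report lagged group 2 against women without cancer. If a direct ratio to group 1 is also quoted, note the small residual excess (about 1.01 to 1.05 in the moderate scenarios), or show the ratio with lag time pooled into group 1 beside it.
6. Do not interpret a complication as contributing to anxiety or depression unless the lagged result supports it.

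The cost is a small change to the time-splitting code, one extra table and two sentences of definition. The downside is that the lagged estimate misses genuine early effects; the unlagged result still shows them.
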